## 7.2 Definition of adverse events and serious adverse events

Adverse event means any untoward or unfavorable medical occurrence associated with the subject's participation in the research, whether or not considered related to the study intervention. Adverse events can be any of the following:

1. Physical signs or symptoms including medication side effects
2. Abnormal laboratory values
3. Changes in vital signs, physical exam findings, or test results
4. An increase in the frequency or intensity (worsening) of a condition or illness that was present before study enrollment.

Serious adverse event (SAE): Any event temporally associated with the subject's participation in research that meets any of the following criteria:

1. Death;
2. Life-threatening (at immediate risk of death);
3. Severely or permanently disabling;
4. Requires in-patient hospitalization or prolongation of existing hospitalization;
5. Pregnancy loss after 20 weeks gestation;
6. Neonatal death up to 6 weeks after delivery;
7. Results in a congenital anomaly/birth defect;
8. Or any event so deemed as serious by the PI at the site.

Note: A "severe" adverse event is not the same as a "serious adverse event" or SAE. Severity is based on the intensity of the event, whereas seriousness is based upon the event outcome as it poses a threat to the patient's life or functioning.

Unexpected, adverse event: An adverse event is considered "unexpected" if it is not listed in the general investigational plan or protocol; or is not listed at the specificity or severity that has been previously observed and/or specified.

## 7.3 Recording of adverse event

All observed or volunteered adverse events (serious or non-serious) and abnormal test findings, regardless of study group or suspected causal relationship to the study intervention(s) will be recorded in the subjects' case report form. Report a diagnosis rather than a symptom. For all adverse events, sufficient information will be pursued and/or obtained so as to permit 1) an adequate determination of the outcome of the event (i.e., whether the event should be classified as a serious adverse event) and; 2) an assessment of the causal relationship between the adverse event and the study intervention(s). Continue to follow each event until it is resolved, stabilizes or until 7 days after the last patient enrolled completes follow-up. Adverse events or abnormal test findings felt to be associated with the study inter-

vention(s) will be followed until the event (or its sequelae) or the abnormal test finding resolves or stabilizes at a level acceptable to the principal investigator.

#### 7.4 Causality and severity assessment

The principal investigator will promptly review documented adverse events and abnormal test findings to determine 1) if the abnormal test finding should be classified as an adverse event; 2) if there is a reasonable possibility that the adverse event was caused by the study intervention(s); and 3) if the adverse event meets the criteria for a *serious adverse event*. The situation surrounding the event should be assessed to determine whether it is related to the study. Record the causality of each event as “possibly related” or “not possibly related”. If causality is unknown, it should be considered “possibly related”.

The maximum intensity of each adverse event should be evaluated and reported as one of the following:

- Mild: events may or may not be volunteered by the patient. The patient is aware of the event, but it is easily tolerated.
- Moderate: signifies discomfort sufficient to interfere with normal activities. A change in therapy may or may not be indicated.
- Severe: side effects are almost always brought up by the patient. These side effects interfere with daily activities and usually require medical intervention.

## 8 CRITERIA FOR INTERVENTION DISCONTINUATION

*List criteria for discontinuing intervention and methods for determining when criteria are met. Include procedures for maintaining subject participation in followup activities.*

The intervention is the performance of PGS on up to 3 blastocysts. It will be discontinued at patient or physician request if the patient is assigned to the PGS group.

## 9 STATISTICAL CONSIDERATIONS

### 9.1 General Design Issues

This is a multicenter randomized controlled trial comparing the benefit and safety of PGS and conventional IVF in women with good prognosis. Subjects will be randomly assigned to 2 parallel groups with 1:1 ratio. This study is designed as a non-superiority study to test the following primary and secondary hypothesis.

- a) The primary hypothesis is that PGS will result in a similar cumulative live birth after up to 3 transfers within 1 year after randomization compared with conventional IVF.
- b) The secondary hypotheses are as follows:
  - 1) PGS will be more likely to yield a Good Birth Outcome.

- 2) PGS will reduce the rate of pregnancy loss.
- 3) The incidence of other maternal and neonatal complications will be comparable between PGS and IVF groups.
- 4) The rate of multiple pregnancy will be comparable between PGS and IVF groups
- 5) The birth weight will be comparable between babies resulted from PGS and IVF.
- 6) PGS will require fewer embryo transfers before achieving live birth.

## 9.2 Outcomes

### 9.2.1 Primary outcome

The primary outcome is the cumulative live birth rate over the (up to) 3 embryo transfers. Live birth is defined as the delivery of any viable infant at 28 weeks or more of gestation after our interventions, and cumulative live birth rate is calculated by dividing the number of women achieving live birth after transfers of all euploid embryos in the PGS group or 3 blastocysts in the IVF group within 1 year after randomization, by the total number of women randomized to the specific group.

### 9.2.2 Secondary outcomes:

The secondary outcomes include the Good Birth Outcome rate (defined as a live birth of an infant born at  $\geq 37$  weeks, with a birth weight between 2500 and 4000g and without a major congenital anomaly), cumulative pregnancy rate, cumulative pregnancy loss rate, multiple pregnancy rate, duration of pregnancy, birth weight, cumulative incidence of maternal and neonatal complications, and number of embryo transfers to achieve live birth.

### 9.2.3 Tertiary outcomes:

The rates of pregnancy, pregnancy loss and live birth after the initial embryo transfer between PGS and IVF.

## 9.3 Sample Size and Accrual

Given the possibility of false positive and the decision of not transferring mosaic embryos which are probably to develop into live birth, we assume that the cumulative live birth rate after transferring PGS-selected euploid embryos will be similar with that after serially transferring all the 3 untested blastocysts. This study is designed as a non-superiority study. It is estimated the cumulative live birth rate after 3 single embryo transfers is 65% in the IVF control group. We set a non-superiority margin at an absolute difference of 7% to retain approximately 90% of the clinical effect of the control group. To be 80% certain that the upper limit of a one-sided 95% confidence interval (CI) of absolute difference between groups to reject null hypothesis that PGS is superior to conventional IVF, 575 pa-

tients were required in each group. In consideration of 5% drop-out rate, a total of 1208 subjects will be enrolled. At present, 8 centers have volunteered and qualified to participate in subjects' enrollment. It is planned that each center will approximately enroll 150 subjects.

#### 9.4 Data Monitoring

We will establish an independent Data and Safety Monitoring Board (DSMB) to review and interpret data generated from the study and to review revisions of the protocol prior to their implementation. Its primary objectives are to ensure the safety of study subjects and the integrity of the research data. The DSMB advises on research design issues, data quality and analysis, and research participant protections for the study. The DSMB will hold regular conference calls in English to review the protocol with respect to ethical and safety standards, monitor the safety of the trials, monitor the integrity of the data with respect to original study design, and provide advice on study conduct. The DSMB will review the progress of the trial, adjudicate adverse events, and decide on any premature closure of the study. The call will be coordinated by the DCC who will provide study updates prior to the call via email.

#### 9.5 Data Analyses

The primary analysis will be performed in accordance with the principle of intent-to-treat. Continuous variables will be described as mean  $\pm$  standard deviation for the normally distributed variables and as median and range for the non-normally distributed variables. Category variables will be presented as frequency and percentage. The differences in the cumulative live birth rate in the two treatment arms will be compared by absolute risk difference and its 95% confidence interval (CI). The relative risk and its 95% CI will also be calculated. Non-superiority of PGS to IVF will be considered to be established if the upper limit of the 95% CI of absolute risk difference was shown to lie below the non-superiority margin of 7%.

The differences in the secondary outcomes such as rate of Good Birth Outcome, cumulative pregnancy rate, cumulative pregnancy loss rate, multiple pregnancy rate obstetric and neonatal complications will be tested by Person chi-square analyses. The absolute difference and 95%CI as well as relative risk and 95% CI will also be calculated. The difference between duration of pregnancy, birth weight and times of embryo transfer will be tested by student t test and non-parameter test if necessary.

The tertiary outcomes such as the rates of pregnancy, pregnancy loss and live birth after the first transfer will be analyzed with Pearson chi-square test. Cost-effectiveness analysis will be done by decision analytic model with TreeAge Pro 2014 (2014 Version; TreeAge

software). Cost effectiveness is defined as an incremental cost effectiveness ratio (ICER). The ICER for live birth was calculated as the difference in cost between two treatment groups divided by the difference in live birth rates between the two groups. The secondary analysis will be performed according to per-protocol analyses. The primary and secondary outcomes will be compared according to actual treatment that subjects received and among subjects who complete embryo transfer(s).

Subgroup analyses will be performed according to different stimulation protocol (e.g. agonist long, agonist short, and antagonist protocol), different endometrial preparation protocol for FET (e.g. natural ovulation cycle and artificial cycle), age groups (e.g. 20~30 group, 30~35 group and >35 group), with or without history of recurrent spontaneous abortion.

Any deviations from the previously described statistical plan will be described and justified in a protocol amendment.

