### **Sample Size and Population**

03/07/2017

We aim to enroll good-prognosis women who are undergoing their first cycle of IVF. The targeted population is women age 20 to 37y, with 3 or more good-quality blastocysts obtained on day 5 of embryo culture. The exclusion criteria are women with a uterine cavity abnormality or women who plan to undergo preimplantation genetic diagnosis (PGD). Given the likelihood of a high proportion of mosaic embryos in the PGS group and our decision to not transfer mosaic embryos (which are unlikely to achieve live birth and have an unknown risk-benefit ratio), we assume that the cumulative live birth rate after the transfer of PGS-selected euploid blastocysts will unlikely exceed that after serially transferring all the 3 untested blastocysts. This study is therefore designed as a non-superiority study. It is estimated the cumulative live birth rate after 3 single embryo transfers is 65% in each group. To be 80% certain that the upper limit of a one-sided 95% confidence interval (CI) would exclude a difference in favor of the PGS group by more than 7%, 575 patients are required in each group. In consideration of 5% drop-out rate, a total of 1208 subjects will be enrolled. The randomization will be stratified by study site. Blocked randomization will be used with dynamic block size. The random number sequence will be generated by the data coordinating center and will be unknown to all investigators. The randomization will be performed on day 5 of embryo culture via a central online randomization system. At present, 8 centers have volunteered and qualified to participate in subjects' enrollment. It is planned that each center will approximately enroll 80 subjects.

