## 5.2 Handling of Study Interventions

Embryo biopsy and NGS will be performed at local sites.

- 1) Embryo biopsy should be completed by the same embryologist at each study site, who has more than 3-years experience to minimize damage on embryos, and different micromanipulators and different laser frequency used in the participating IVF centers are allowed. Biopsy should be performed on Day 5 of embryo culture when blastocysts reach score 4BC or better and fully expand. The biopsy site should be right opposite to the ICM and only 3-5 herniating TE cells will be aspirated. After the operation, survival

03/07/2017

of the embryo is regarded as a success and operation time should be recorded. Patient's name, the medical record number and embryo number should be clearly marked to ensure the consistency.

- 2) Different NGS platforms (*Illumina MiSeq/NextSeq550 or Life Tech PGM/Proton*) applied in different IVF centers are allowed. This reflects current practice where different platforms are used. The resolution value is defined as 4Mb. For laboratory environment and facilities, reagent preparation district, WGA preparation district, library preparation district, product purification district and sequencing district should be separated to prevent contamination and buffering area should be set between the adjacent districts. For laboratory technicians, professional training and technical competence is required. For WGA, first, sample-positive control and negative control are necessary; Second, concentration of products detected using Qubit assay should be no less than 20ng/  $\mu$ l, and those of negative control should be less than 10ng/  $\mu$ l; Third, two technicians are needed to prevent confusion when to transfer samples between tubes. For library preparation, the concentration should be more than 0.5 ng/  $\mu$ l and the volume should be no less than 20  $\mu$ l. For sequencing results, the quality control standard of different platforms should be established and complied with. For example, based on Proton of Life Tech, the loading rate should be more than 60%, polyclone rate no more than 40%, low quality rate no more than 30%, and reads counts of each sample larger than 1M. In the last, all operations should be completed by two technicians together in the lab and auditors should audit the original data and check the sequencing report.

This is an open-label unblinded trial because it is not possible to mask the embryo biopsy.

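### Randomisation is stratified by site but no planned primary or binary analysis names site: a minor gap, free to close, costing a little efficiency only if live-birth rates differ between sites

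*Combined protocol and SAP*

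**What the plan says.** **Randomisation.** Synopsis, Sample Size and Population: "The randomization will be stratified by study site" and "Blocked randomization will be used with dynamic block size". Section 9.1: "Subjects will be randomly assigned to 2 parallel groups with 1:1 ratio". Site is the only stratification factor named.

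**Analysis.** Under section 9.5 the cumulative live birth rates in the two arms "will be compared by absolute risk difference and its 95% confidence interval (CI", with a relative risk and its CI alongside. Non-superiority is declared if the upper limit of the 95% CI lies below 7%. Binary secondary outcomes and the first-transfer tertiary outcomes are tested by Pearson chi-square. The section names no site stratum, weighting, covariate or random effect, and site is not among the subgroups. It gives no formula for the interval of the risk difference.

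**Final analysis.** The Final statistical analysis text uses a two-sided 90% CI for the primary hypothesis and names no site term. The Summary of changes reports only the change of CI level.

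**Sample size.** Synopsis: "It is estimated the cumulative live birth rate after 3 single embryo transfers is 65% in each group", and "To be 80% certain that the upper limit of a one-sided 95% confidence interval (CI" would exclude a larger advantage for PGS than the margin. Section 9.3: "We set a non-superiority margin at an absolute difference of 7" percentage points. The result is 575 per group, and 1208 in total with 5% drop-out.

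**The concern.** Blocking within site keeps the arms nearly balanced on site, so the true sampling variance of the risk difference contains only within-site variation. A variance computed as if there were no strata still counts between-site variation as error. When sites differ in live-birth rate, the interval is therefore wider than it needs to be and the test runs below its nominal level.

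Site differences are plausible here. Sections 5.3 and 5.3.1 leave the stimulation protocol, endometrial preparation and luteal support to the local investigator or local routine, and these apply to both arms. At stake is a small amount of precision in the single interval that decides the trial, whose sample size was set at the minimum for 80% power.

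**Working it through.** **Inputs from the documents:** live birth rate 0.65 in each group, margin 0.07, one-sided alpha 0.05 (z = 1.6449), power 0.80 (z = 0.8416), 575 per arm, 8 centres.

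**Input not in the documents:** the between-site SD of the live-birth rate. I assume 3 to 10 percentage points, with 0 as reference.

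**1. The plan's own figure.** Per-woman variance is 0.65 × 0.35 = 0.2275. Then n = (1.6449 + 0.8416)² × 2 × 0.2275 / 0.07² = 574.1, rounded up to 575. The total is 2 × 575 × 1.05 = 1207.5, rounded up to 1208. Both match, and neither uses a site term.

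**2. Unstratified interval.** SE = √(2 × 0.2275 / 575) = 0.02813. The half-width is 4.63 points for a 90% CI and 5.51 points for a 95% CI.

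**3. Share of variance due to site.** f = SD² / 0.2275, and the stratified SE is the crude SE multiplied by k = √(1 − f).

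**4. Type I error of the unstratified test.** Its statistic has standard deviation k rather than 1, so the actual level is Φ(−1.6449 / k).

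**5. Power at 575 per arm.** With 0.07 / 0.02813 = 2.4884:
- unstratified: Φ((2.4884 − 1.6449) / k)
- stratified: Φ(2.4884 / k − 1.6449)

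The reduced sampling variance must be used for both tests, because both follow the same stratified randomisation.

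**6. Women needed per arm for 80% power.**
- unstratified: 0.455 × ((1.6449 + 0.8416k) / 0.07)²
- stratified: 574.1 × (1 − f)

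The total saving is the difference × 2 × 1.05.

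| | SD 0 | SD 3 points | SD 10 points |
|---|---|---|---|
| f | 0 | 0.0009/0.2275 = 0.4% | 0.01/0.2275 = 4.4% |
| k | 1 | 0.9980 | 0.9778 |
| Interval narrower by | 0 | 0.2% | 2.2% |
| 90% half-width, stratified | 4.63 | 4.62 | 4.52 |
| 95% half-width, stratified | 5.51 | 5.50 | 5.39 |
| Level of unstratified test | 5.0% | 4.97% | 4.6% |
| Power, unstratified | 80.1% | 80.1% | 80.6% |
| Power, stratified | 80.1% | 80.2% | 81.6% |
| n per arm, unstratified / stratified | 574.1 / 574.1 | 573.3 / 571.8 | 565.5 / 548.9 |
| Women saved in total | 0 | 1.5 × 2.1 ≈ 3 | 16.6 × 2.1 ≈ 35 |

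**7. Simulation check** (8 equal sites, 72 women per arm per site, 40,000 runs). With no site variation, type I error at the margin is 5.1% for both analyses. At SD 10 points (site rates about 50% to 80%) it is 4.6% unstratified and 5.0% stratified. Power there is 80.5% and 81.65%, in line with step 5.

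The level, power and patient figures are for the one-sided 5% test, that is, the two-sided 90% CI of the final analysis. They do not describe the two-sided 95% CI rule in section 9.5, under which power at 575 per arm is about 70% with no site variation. That gap is a separate matter and much larger than this one.

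**The case against.** The strongest reply is that nothing here threatens validity. The unstratified analysis is neutral to mildly conservative, so site cannot push the risk of a false non-superiority claim above nominal. The 575 per arm reproduces without any site term, so the stated power does not rely on a stratified analysis. All of that stands.

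Second, the size of the effect is unknown. The documents report no live-birth rates by site, and eligibility narrows the case mix: age 20 to 37, first cycle, at least 3 good-quality blastocysts, with ICSI and freeze-all for everyone. This also stands, and it is why the conclusion is conditional.

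Third, not all local variation is relevant. Section 5.2 says different sequencing platforms "applied in different IVF centers are allowed", and biopsy equipment may also differ, but these touch only the PGS arm. They point to site-specific treatment effects rather than to a shared site baseline. I therefore rest the case on stimulation, endometrial preparation and luteal support.

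Fourth, section 9.5 gives no interval formula, so for the primary outcome an unstratified interval is the natural reading rather than a stated fact. Only the Pearson tests are explicitly unstratified. This stands too, and naming the method would settle it.

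None of these points is a reason to leave the strata out. In the simulation, stratifying cost essentially nothing when sites were alike and held the nominal level when they differed widely.

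**Conclusion.** This is a free improvement of minor weight. The plan stratifies randomisation by site and then names no site term in its primary or binary analyses. Under an assumed between-site SD of 3 to 10 points, the loss is about 0.2% to 2.2% of interval width, 0.1 to 1.0 points of power, and roughly 3 to 35 women in total. It is zero if sites do not differ.

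A reader might infer more, and the documents do not support it:
- **That the intervals are certainly too wide.** This depends on a between-site SD that the documents do not give.
- **That the crude result is invalid or its type I error inflated.** The error goes the other way: about 5.0% at SD 3 and 4.6% at SD 10.
- **That power would rise from 80.1% to 81.6% at SD 10.** That comparison denies the unstratified test the variance reduction that stratified randomisation gives it. Its power at SD 10 is already 80.6%.
- **That adjusting for age would add a known gain.** Age is collected and used for subgroups, but the documents contain nothing from which a gain could be calculated.

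**What to change.** In section 9.5:
- Make the primary estimate the Mantel-Haenszel risk difference stratified by study site, with its CI and the method named. Report the relative risk in the same way.
- Use Cochran-Mantel-Haenszel tests stratified by site for the binary secondary outcomes and for the tertiary outcomes.
- Keep the crude risk difference as a sensitivity analysis.
- Standardisation for baseline age (a marginal risk difference) may be added as an option, with no gain claimed.

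The cost is one paragraph of the SAP and a few lines of code. Site is already held for randomisation, so no new data are needed, and the sample size need not change.

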## 2.2 Supporting Data

In vitro fertilization (IVF) is a well-established technology for infertility treatment, but IVF does not guarantee success. In the U.S. the live birth rate was 27.3% after fresh embryo transfer and 31.5% after frozen embryo transfer from the ART (Assisted Reproductive Technology) Success Rates tabulated by the Centers for Disease Control and Prevention (CDC) of the United States report in 2013. Traditionally, multiple embryos are transferred to improve pregnancy rates, but this has also resulted in a high rate of iatrogenic multiple pregnancy, which is still one of the major complications of IVF. Elective single embryo transfer (eSET) has been introduced as the most effective way to minimize the multiple pregnancy rate. As a consequence, embryo selection becomes crucial to maintain the pregnancy and live birth rates after decreasing the number of embryos transferred. Embryo aneuploidy is thought to be one of the main causes of implantation failure, preimplantation growth arrest, and spontaneous abortion. A randomized trial demonstrated that the ongoing pregnancy rate (>24 weeks) was comparable between transferring a single euploid blastocyst and transferring two untested blastocysts. However, conventional morphological score does not predict the genetic conditions of embryos.

The embryo aneuploidy rate increases steadily with age. However, the embryo aneuploidy rate was also suggested to be high in young patients. Franasiak et al. reported that the aneuploidy rate was 34.15% in patients under 26 years, and 33.99% in patients aged 30 to 38. The average rate of aneuploidy in women under 38 years was 58.9% with blastomere biopsies and 36.1% with blastocyst biopsies. There was also a report that the aneuploidy rate in patients under 35 years was as high as 44.9% (191/425). PGS is proposed as a potentially effective approach to facilitate embryo selection and eventually improve the singleton live birth rate.

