#### *Rationale for morphologic scoring on embryos*

Embryo morphologic assessment is the most commonly used method for embryo selection in the clinical routine. The three-part scoring system for blastocysts was developed in 1999 based on blastocyst expansion, inner cell mass (ICM), and trophoctoderm (TE) development. Using this scoring system it was revealed that there was a strong correlation between the clinical outcomes (implantation rates, pregnancy)

03/07/2017

and the morphological grade of blastocysts, and the transfer of top-scoring blastocysts produces increased implantation and pregnancy rates.

Although this type of selection is simple and direct, there are also many limitations. The main limitation is that it is a static system and can be operator-dependent. More importantly, it is unable to validly reflect the chromosomal status of the embryos. Although there seems to be a relationship between the ploidy status and blastocyst morphology, the euploid embryo rate was only 40% -56% in the top-scoring blastocysts, and miscarriage rate wasn't effectively improved after the transfer of top-quality ones. Thus, morphologic evaluation alone cannot meet the growing demands for embryo selection, especially in the context of SET.

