#### Pre-Entry

During ovarian stimulation, ultrasonography and serum steroid hormone assays will be performed at the local study site. Ovarian hyperstimulation syndrome as well as other adverse events will be recorded. Subjects whose cycles are cancelled, who have no oocytes, or who experience no fertilization will not be eligible for randomization. On day 3 of embryo culture, embryo number and morphological score will be recorded. On day 5 of embryo culture, embryo number and morphological score will be recorded again. Women with less than 3 good-quality blastocysts will not be randomized.

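### The primary risk difference is unadjusted for site, age and the embryo number and grade recorded before randomisation, which forgoes a small and almost free gain in precision

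*Combined protocol and SAP*

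**What the plan says.** Section 9.5 states that the cumulative live birth rates of the two arms "will be compared by absolute risk difference and its 95% confidence interval (CI"). Section 9.2.1 makes each rate a simple proportion, the women with a live birth divided "by the total number of women randomized to the specific group". Non-superiority is declared if the "upper limit of the 95% CI of absolute risk difference was shown to lie below the non-superiority margin of 7" percent. No regression model, standardisation or stratified estimator is named in 9.5, on the opening analysis page, or in the Final statistical analysis text at the end of the document. Age appears only as a subgroup factor.

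The candidate covariates exist before allocation. Under Pre-Entry (6.2.1), embryo number and score are recorded on day 3, and then: "On day 5 of embryo culture, embryo number and morphological score will be recorded again". This scoring has to come before randomisation, because eligibility under 4.1.3 depends on it. Age is known at screening. The Synopsis (Sample Size and Population) gives site as the only stratification factor.

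The background treats grade and age as relevant. The rationale for morphologic scoring reports that "there was a strong correlation between the clinical outcomes (implantation rates, pregnancy") and blastocyst grade, and section 2.2 says "The embryo aneuploidy rate increases steadily with age".

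**The concern.** The primary conclusion turns on one confidence limit falling below 7 percentage points. Baseline variables that predict live birth add variation to a crude difference. A standardised risk difference from a model with pre-randomisation covariates removes the part they explain. It estimates the same marginal difference, so the 7-point margin needs no change. Site is used to balance allocation and then dropped from the analysis. If site predicts outcome, the crude interval is, if anything, slightly too wide. What is at stake is a modest amount of precision on the decisive limit.

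**Working it through.** **Inputs from the documents.** 65% live birth in each group, a 7-point margin, 80% power and a one-sided 95% limit, since the Synopsis wants to be sure that "the upper limit of a one-sided 95% confidence interval (CI) would exclude a difference in favor of the PGS group by more than 7" percent; 575 per group, 5% drop-out, 1208 in total (Synopsis and 9.3).

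**Reproducing the plan's figure.** n per group = 2 × 0.65 × 0.35 × (1.645 + 0.842)² / 0.07² = 574.1, rounded up to 575. Drop-out: 1150 × 1.05 = 1207.5, rounded up to 1208. Both match. The stated size therefore rests on an unadjusted comparison at one-sided 5% and takes no credit for covariates.

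**Crude precision.** SE = √(2 × 0.65 × 0.35 / 575) = 2.813 points. Distance from estimate to upper limit = 1.645 × 2.813 = 4.63 points. Power at a true difference of zero = Φ(7/2.813 − 1.645) = about 80.0%.

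**Effect of adjustment.** To a good approximation, the variance of the standardised difference is the crude variance times (1 − R²), where R² is the share of outcome variance explained by the covariates. The documents give no R², so 1% to 10% is an assumption. For a single baseline score, R² of about 1%, 2% and 5% corresponds to an AUC of about 0.56, 0.58 and 0.63. Extra women per group = 575/(1 − R²) − 575.

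| Assumed R² | SE (points) | Distance to upper limit (points) | Largest observed difference that still passes (points) | Power | Equivalent extra women per group |
|---|---|---|---|---|---|
| 0 (crude) | 2.813 | 4.63 | 2.37 | 80.0% | – |
| 1% | 2.799 | 4.60 | 2.40 | 80.4% | 6 |
| 2% | 2.785 | 4.58 | 2.42 | 80.8% | 12 |
| 5% | 2.742 | 4.51 | 2.49 | 81.8% | 30 |
| 10% | 2.669 | 4.39 | 2.61 | 83.6% | 64 |

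If the 95% interval in 9.5 is read as two-sided, the distance starts at 5.51 points and power at 70.1%. Adjustment at the same four R² values gives 70.6%, 71.0%, 72.3% and 74.6%.

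**Simulation check.** 2000 trials were simulated with 575 per group, one baseline score and a standardised logistic estimate. The ratio of adjusted to crude variance was 1.00 for a useless covariate, 0.99 at R² of about 2% and 0.95 at about 5%. This agrees with the formula and shows no material penalty if the covariate turns out to be uninformative. The simulation did not include site terms.

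**Can the model carry the terms?** With the 8 centres named at present, the model needs treatment (1), site (7), age (1), blastocyst number (1) and a grade summary (1), which is 11 terms. At 65% live birth, about 0.35 × 1150 = 402 women have no live birth, or roughly 37 per term.

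**The case against.** The strongest reply is that nothing here is wrong. The crude intention-to-treat difference is valid, the design and analysis agree, and the planned 80% power does not depend on covariates. That stands in full.

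The second reply is that the gain may be near the bottom of the range, and the documents support this:
- Age is limited to 20 to 37. One series cited in 2.2 shows flat aneuploidy (34.15% under 26 years, 33.99% at 30 to 38), despite the general statement about age.
- The reported correlation is between grade and implantation or pregnancy, not cumulative live birth per woman over up to three transfers. The same section calls grading static and operator-dependent.
- Entry requires at least three blastocysts of 4BC or better, which narrows the spread.

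These points limit the size of the benefit. They do not remove it, because the cost is also close to nil.

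A reader might infer more than the documents support:
- **That the crude estimate is biased by chance imbalance in age or embryo quality.** Randomisation makes such imbalance part of the sampling variance that the interval already covers. Imbalance and interval width are one harm, not two.
- **That power of 70.1% under the 95% rule is due to the missing covariates.** That comes from the interval level, a separate matter. The Final statistical analysis text uses a two-sided 90% interval, which matches the sample-size basis.
- **That AMH could be added because every woman has it.** The schedule of evaluations lists AMH, but the baseline assay list in 6.3.6 does not.
- **That the same adjustment suits pregnancy loss.** The rationale for morphologic scoring says miscarriage was not effectively improved by transferring top-quality blastocysts. Loss among pregnancies also has a denominator formed after randomisation.

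**Conclusion.** The point holds as an efficiency recommendation. The primary analysis leaves unused information that is collected before allocation in every randomised woman. Using it would shorten the distance to the decisive limit by about 0.02 to 0.24 points (one-sided 5%) and raise power by about 0.4 to 3.6 percentage points. This rests on an assumed R² of 1% to 10%, 65% live birth in both groups, 575 women per group, and covariates fixed in advance. The lower part of the range is plausible given the eligibility criteria. The documents do not support calling the planned test invalid or the trial underpowered on this ground.

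**What to change.** In 9.5, and in the matching text on the opening analysis page, state:
- The primary estimate is the marginal (standardised) risk difference from a logistic model with treatment, study site, maternal age (continuous), number of good-quality day-5 blastocysts, and one pre-specified summary of day-5 grade. An example is how many of the three best blastocysts have trophectoderm A or B.
- All covariates are taken as recorded before randomisation. The rule that ranks the three best is fixed in advance.
- The interval is robust or bootstrap. The 7-point margin and the interval level are unchanged.
- The crude risk difference is reported alongside.
- No post-randomisation variable, such as endometrial preparation, enters the model.

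The same model may be used for first-transfer live birth per woman randomised. It should not be extended to pregnancy loss among pregnancies. A conditional odds ratio would not do as the primary estimate, because the margin is an absolute difference.

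The cost is a paragraph of analysis-plan text, agreement on the coding of grade, and a short program. No new data and no extra women are needed.
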